### Power analysis and statistical analysis

Sample size for expected difference in the primary outcome was based on pilot trials. Effect size of treatment on various outcomes, including motor skills, was 0.48 mean of the standard deviation (SD), with 95% CI = 0.10 to 0.85. As for quality of life and mood, we aimed at detecting clinically significant changes induced by moderate physical exercise. In a recent meta-analysis, moderate-to-vigorous physical exercise was associated with a medium effect size of 0.64 (95% CI, 0.27 to 1.01) in reducing depressive symptoms [26]. Overall, we expect that the experimental intervention could produce a change in the exposed group with an effect size of 0.45 SD. We have determined, by a test of difference between proportions, that a sample of 60 participants per group is required to achieve 80% power to detect a difference with a medium effect size *h* = 0.45, at a two-sided significance level of 0.05. It means that at the estimated power, risk reduction is 0.215, and number needed to treat (NNT) = 5.

The main outcome measures and expected improvement are the following: SF-12 score (10%), walking speed (10%), and postural sway area (20%). Differences in the primary outcomes will be analyzed with a two-tail test for proportions with the Miettinen exact test. A multiple logistic regression will be performed to treat the confounding factors and control the impact of the confounding variables (sex, age, co-morbid condition, previous exercise activity) on outcomes. Survival analyses will be carried out using the Kaplan-Meier curve. Data will be analyzed at the individual level, and clustering (participants having been exposed to the intervention in groups) will be not accounted for in the analysis. Analysis by treatment allocated will be used considering both primary and secondary outcomes. The analysis by treatment allocated will include all participants for which there is data at t0. There will be no interim analyses planned for efficacy or safety since this is a short trial with no administered drug. Analyses will be done with Excel or the Statistical Package for Social Science (SPSS).

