To date, most studies on the effectiveness of PA protocols in the elderly were based on trials conducted on small samples, rarely with randomized control designs and still with contradictory indications on timing and optimal method of administration (even though both anaerobic and aerobic activities seem to be useful). While the use of subjective/non-instrumental evaluations in the assessment of motor function outcomes is widespread, the amount of available data from dedicated laboratory equipment—able to provide reliable measures of gait and balance—is limited [8]. Animal studies have shown that PA may influence brain functions through altered blood flow, reduce age-related neuronal loss, and stimulate de-novo synthesis of neurons. These mechanisms might be based on increases in growth factors, neuropeptides, and endorphins [7]. Studies in animals have recently focused on the insulin-like growth factor-1 (IGF-1), which was found upregulated in the brain and the periphery after PA [9]. There is evidence that PA can positively influence the quality of life in the elderly [10], and can improve as well symptoms of depression [11], frequently observed in old people. There is also evidence that acute intense exercise can increase CD4+ and CD8+ T lymphocytes in senescent naïve memory and promote markers of cellular aspects of the immune system in elderly subjects [12]. However, most studies have involved small samples, are based on an acute bout of exercise, and often lack adequate follow-up, and they do not generally provide clarifications as to whether PA can contrast immunosenescence, i.e., the progressive dysfunction of the immune system in the elderly that leads to increased susceptibility to infections and autoimmune disease.

This study set up to investigate (a) whether a moderate activity can be as effective as intense activity in older people. The available studies did not provide an intervention model based on moderate activity, even though this could be the only option viable for the elderly with some medical conditions; (b) the mutual influence of the different variables involved through complex multidisciplinary perspectives (which has been rarely done so far).

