This study aims at assessing the effects of moderate PA on an elderly sample’s QoL, biological rhythms (sleep/wake; nutrition and daily life activities), depressive dysfunctional attitudes, static-dynamic balance, cognitive functioning, and at determining the occurrence, if any, of adverse events that are possible in elderly people while performing PA. The study also aims at testing the relationships of such outcomes with the increase of melatonin, IGF-1, and immune response in the blood and to verify the relationships of PA with community assets (settings, mobility safety, social cohesion). The study design includes a control condition that is not expected to provide relevant effects on the main outcomes, although by effect of sociality and the formation of social bonds during the recreational activities, it is still possible that a fraction of the participants may benefit in terms of QoL. The effects of the control condition on the physiological parameters are less likely. In particular, we expect that the PA intervention, but not the control condition focused on recreational activities, will impact on the immune system by improving some of the measures that have been selected to assess its functioning: measurements of IgG, IgA, and IgM; T cells response to mitogens such as PHA and cytometric analysis of the Th1, Th2, and Th17 subsets.

Given the social and economic importance of the issue of disability in the elderly, our results could have a major impact on future practices. The main outcomes of the project are related to the availability of a standardized model of intervention in the real life, while the secondary objectives will provide a set of heuristic hypotheses in a research field defined as a priority for the next Horizon calls. A general objective of the project is also to increase the multi-disciplinary skills and the attitude to joint work in a field that is a primary recipient of EU funding.

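### The stated 80% power for an effect of 0.45 with 60 per group is about 69% at two-sided 0.05, and for SF-12 the 0.45 itself is weakly defined and indirectly supported

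*Protocol article*

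**What the plan says.** All the planning figures stand in the protocol article, section Power analysis and statistical analysis.

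- Pilot evidence: "Effect size of treatment on various outcomes, including motor skills, was 0.48 mean of the standard deviation (SD), with 95% CI = 0.10 to 0.85". The text does not say whether SF-12 was among these outcomes, or whether the figure is a between-arm contrast.
- Evidence introduced for quality of life and mood: "moderate-to-vigorous physical exercise was associated with a medium effect size of 0.64 (95% CI, 0.27 to 1.01) in reducing depressive symptoms".
- Planning effect: "we expect that the experimental intervention could produce a change in the exposed group with an effect size of 0.45 SD".
- Sample size: "a sample of 60 participants per group is required to achieve 80% power" "to detect a difference with a medium effect size", with h = 0.45, "at a two-sided significance level of 0.05". The paragraph restates this as a risk reduction of 0.215 and an NNT of 5.

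The paragraph gives no separate power for any single outcome. The section Primary outcomes lists SF-12, walking speed and postural sway area. SF-12 alone has two primary time points, end of treatment and end of follow-up.

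The section on the control condition (Educational and leisure activities) says the comparator is meant to match the social side of the exercise sessions. The Discussion expects no material effect of the control on the main outcomes, but adds, through sociality and bonding, that "it is still possible that a fraction of the participants may benefit in terms of QoL". It regards control effects on physiological measures as less likely.

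**The concern.** There are two separate difficulties.

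The first is arithmetic. The effect, significance level, sidedness, group size and power are all stated, and they do not agree with one another. A reader who relies on the 80% would think a true effect of 0.45 has a 20% chance of being missed, when the chance is nearer 31%. A null result on any primary outcome could then be given more weight as evidence of no benefit than the design supports.

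The second concerns what the 0.45 measures, and bears mainly on SF-12. The number is described as a change in the exposed arm, and the next sentence uses it as the difference between two arms. The two are equal only if controls do not change. SF-12 is self-reported, and quality of life is the one outcome on which the protocol itself allows that the social control may help. It is also the outcome for which no effect size of its own is quoted. If part of the 0.45 is shared with controls, the contrast actually tested is smaller and power falls below 69%.

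**Working it through.** **Inputs** (Power analysis and statistical analysis): h = 0.45; n = 60 per group; two-sided alpha 0.05, so z = 1.960; power 80%, so z = 0.842. Allocation is 1:1 (Randomization).

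**1. The plan's own figure.** The arcsine method for two proportions gives

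n per group = 2 × ((1.960 + 0.842) / h)²

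With h = 0.45: 2 × (2.8016 / 0.45)² = 77.5, so 78 per group, 156 in total. The stated 60 is not reproduced.

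**2. Power at 60 per group.**

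Power = Φ(h × √(n/2) − 1.960) = Φ(0.45 × √30 − 1.960) = Φ(2.465 − 1.960) = Φ(0.505) = 69.3%

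The chance of missing the effect is therefore 100 − 69.3 = 30.7%, against the 20% implied.

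**3. Does another method rescue 60?**

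- t-test on a difference of 0.45 SD: 68.6%.
- Pooled test at the proportion pairs that fit both h = 0.45 and a difference of 0.215 (0.262 vs 0.477, or 0.523 vs 0.738): 68.9%, with 78 per group needed for 80%.
- The same pairs with continuity correction: 88 per group.
- One-sided 0.05 (z = 1.645): 2 × ((1.645 + 0.842) / 0.45)² = 61.1, so 62 per group, and 79.4% power at 60.

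Only the one-sided calculation comes close to the stated pair of 60 and 80%. The protocol specifies a two-sided level and a two-tailed test. Why the figures match a one-sided test cannot be known from the document.

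**4. Effect that 60 per group does detect.** 2.8016 × √(2/60) = 0.511, so about h = 0.51 for 80% power at two-sided 0.05.

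**5. The quoted evidence as the effect.** At the pilot value of 0.48, power is Φ(0.48 × √30 − 1.960) = 74.8%, still short of 80%. At the meta-analysis value of 0.64 it is 93.9%, but that outcome is depressive symptoms.

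**6. SF-12 sensitivity (assumption only).** Suppose 0.45 SD is the exposed-arm change and controls gain g SD. The net effect is then 0.45 − g, and power = Φ((0.45 − g) × √30 − 1.960). The protocol gives no value for g, so the rows below are illustrations.

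| Assumed control gain g | Net effect | Power at 60 per group | n per group for 80% |
|---|---|---|---|
| 0 | 0.45 | 69.3% | 78 |
| 0.10 | 0.35 | 48.3% | 129 |
| 0.20 | 0.25 | 27.7% | 252 |

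**The case against.** The strongest reply is to the SF-12 part.

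**Control gain.** A reader might infer that the protocol expects controls to gain quality of life and fails to subtract it. The Discussion does not say that. It expects no relevant control effect on the main outcomes and treats a benefit in some participants as a possibility. This objection stands: no control gain can be read off the document, and no loss of power below 69% can be shown from it.

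**Between-arm reading.** A reader might also infer that 0.45 is definitely a within-group change. The paragraph speaks of an effect of treatment, a difference to detect, a risk reduction and an NNT, all natural terms for a contrast between arms. The pair h = 0.45 and 0.215 also implies that about 26% or 52% of controls respond, so some control improvement is compatible with the design figures. This stands to the extent that the within-group reading is not proven. It does not remove the ambiguity: the risk reduction and NNT are presented as consequences of h, so they show how 0.45 was used, not where it came from.

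**Cautious planning value.** The 0.45 lies below both the pilot 0.48 and the meta-analysis 0.64, and the latter is direct evidence for mood. That is fair. But the pilot value also falls short of 80% power at 60 per group, and neither source is shown to concern SF-12.

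**Timing.** The abstract reports 120 participants as already randomized, so the sample size is settled. That limits the remedy to reporting and does not make the stated power right.

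None of these replies touches the arithmetic in steps 1 to 4, which takes 0.45 as a true between-arm effect with no control gain.

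**Conclusion.** The point holds in two parts of unequal strength.

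The 80% is overstated. At h = 0.45, two-sided 0.05 and 60 per group, power is about 69% (68.6% to 69.3% by method). It would take 78 per group to reach 80%, and the design detects about h = 0.51. This rests only on figures in the protocol and applies to all three primary outcomes.

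For SF-12 the planning effect is less secure than for the motor outcomes. Its wording leaves open which contrast it measures, the support named for quality of life is indirect, and the protocol allows for some control benefit on this outcome. How far SF-12 power lies below 69%, if at all, cannot be determined. The 48% and 28% figures are conditional on assumed control gains of 0.10 and 0.20 SD and should not be read as estimates of the trial's power.

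**What to change.** In Power analysis and statistical analysis:

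1. Replace the 80% claim with about 69% power at h = 0.45 for 60 per group at two-sided 0.05, or state instead that 60 per group gives 80% power for about h = 0.51.
2. Define 0.45 explicitly as the difference between arms, or say that it is not one.
3. Say that the depression meta-analysis is indirect support for an effect on SF-12, and whether the pilot figure included SF-12.
4. Give SF-12 power over a range of smaller net effects, labelled as an assumption, for example 48% at 0.35 and 28% at 0.25. Say whether the same range is meant to apply at both SF-12 time points.

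The cost is a less favourable stated power and a few sentences of text. No extra participants are needed and the analysis does not change.

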### Randomization

Randomization will be conducted at the University of Cagliari after baseline assessment. Randomization will be computer-based and concealed. The people who will conduct the randomization procedure are blind to the participants’ identities and status and will not receive any information on the participants. Randomization will be by blocks of randomized permutations to experimental treatment with a 1:1 rate; codes will be masked.

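### Sixty per group give 69% power, not 80%, for h = 0.45 at two-sided 0.05; 80% power needs 78 per group

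*Protocol article*

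**What the plan says.** In the protocol article, the section on power analysis and statistical analysis fixes every input of the calculation:

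- The sizing method is a comparison of two proportions: "We have determined, by a test of difference between proportions".
- The target is a "medium effect size *h* = 0.45". It follows a sentence expecting that the intervention "could produce a change in the exposed group with an effect size of 0.45 SD".
- The result is that "a sample of 60 participants per group is required to achieve 80% power to detect a difference with a medium effect size", "at a two-sided significance level of 0.05".
- The consequence drawn is that "at the estimated power, risk reduction is 0.215, and number needed to treat (NNT) = 5".
- The analysis is two-sided as well: "Differences in the primary outcomes will be analyzed with a two-tail test for proportions with the Miettinen exact test".

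The Randomization section gives equal allocation ("randomized permutations to experimental treatment with a 1:1 rate"), and the abstract gives 120 participants in total. The two response proportions behind h are not stated, and the calculation states no allowance for loss of participants.

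**The concern.** Effect size, group size, level, sidedness and power are all given, and any four of them determine the fifth. The response rates are not needed for a first check, because h is the difference of arcsine-transformed proportions and its variance does not depend on the rates. At a two-sided 0.05 level, 60 per group looked too few for 80% power at h = 0.45.

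The stated power is the yardstick for reading a non-significant result. If the true figure is near 70%, the risk of missing the targeted effect is about half as large again as the protocol implies, and a null result judged against 80% would be taken as stronger evidence of no benefit than it is. The risk reduction and number needed to treat are presented as what the trial can detect at that power, so they carry the same fault.

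**Working it through.** **Inputs**, all from the protocol's power section except allocation (Randomization section): h = 0.45; n = 60 per group; 1:1; alpha = 0.05 two-sided; power 80%. Normal quantiles: 1.960 (two-sided 0.05), 1.645 (one-sided 0.05), 0.842 (80% power).

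**Step 1. Try to reproduce 60 per group as described (two-sided).**
n = 2 × (z_alpha + z_beta)² / h² = 2 × (1.960 + 0.842)² / 0.45² = 77.5, so 78 per group or 156 in total. The stated 60 is not reproduced.

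**Step 2. Power at 60 per group, two-sided.**
Power = Φ(h × √(n/2) − 1.960) = Φ(0.45 × √30 − 1.960) = Φ(0.505) = 0.693.

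**Step 3. Effect detectable with 80% power at 60 per group.**
h = (1.960 + 0.842) × √(2/60) = 0.511.

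**Step 4. Look for a calculation that does give 60.** With a one-sided 0.05 level:
- n = 2 × (1.645 + 0.842)² / 0.45² = 61.1, so 62 after rounding up;
- power at 60 is 79.4%;
- the h detectable with 80% power at 60 is 0.454, which rounds to 0.45.

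This is close to the protocol's figures, though not an exact match.

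**Step 5. Check without the arcsine approximation.** Two pairs of rates satisfy both h = 0.45 and a risk difference of 0.215: 0.262 vs 0.477, and 0.523 vs 0.738. Exact enumeration of the pooled z test with 60 per group gives 69.2% two-sided power for each pair (80.4% one-sided).

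**Step 6. Other two-sided readings at 60 per group.**

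| Reading | Power at 60 per group | n per group for 80% |
|---|---|---|
| Pooled-proportion formula, h = 0.45, lower rate 0.05 to 0.90 | 59% to 69% | 78 to 98 |
| Exact score or Miettinen-Nurminen test, h = 0.45, lower rate 0.02 to 0.70 | 66% to 71% | not computed |
| Fisher exact test, same rates | 49% to 64% | not computed |
| t-test, 0.45 SD | 68.6% | 79 |
| t-test, pilot value 0.48 SD | 74.1% | 70 |

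None reaches 80%. A continuity correction raises the pooled-proportion n to 87 or more.

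**Step 7. Does the risk difference of 0.215 rescue the claim?** Held fixed, it gives about 80% two-sided power at 60 per group only at more extreme rates, such as 0.13 vs 0.345 (79.8%) or 0.65 vs 0.865 (79.2%). Those pairs have h = 0.518 and 0.514, not 0.45.

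**Step 8. Risk difference at a true 80% power.** With h = 0.511, a control rate of 0.262 gives 0.508 in the other arm, a difference of 0.246. A control rate of 0.523 gives 0.765, a difference of 0.242. The reciprocals are 1/0.246 = 4.07 and 1/0.242 = 4.13, against 1/0.215 = 4.65 for the protocol's own figure.

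**Step 9. Illustration of losses.** Assume 10% or 20% of participants drop out of the analysis (rates not in the protocol). Then n = 54 or 48 per group, and power is Φ(0.45 × √27 − 1.960) = 65% or Φ(0.45 × √24 − 1.960) = 60%.

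**The case against.** The main arithmetic is not open to dispute: both the sizing sentence and the analysis sentence are two-sided. The objections concern what is built on it.

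- **One-sided origin.** The protocol never mentions a one-sided test, and the one-sided requirement is 62, not 60. This stands. The one-sided explanation is a plausible inference and no more.
- **Risk difference and number needed to treat.** A difference of 0.215 is compatible with h = 0.45, and 1/0.215 = 4.65 rounds to 5, so these are not separate errors. This stands; only their pairing with 80% power fails. The replacement difference depends on a control rate that the protocol does not give. If 4.07 or 4.13 is rounded up, the number needed to treat remains 5.
- **Losses.** The protocol analyses everyone with baseline data and carries the last observation forward, so the analysed number stays at 60 per group. This stands against reading 65% and 60% as predictions. It does not restore power, because a carried-forward baseline value shows no improvement and dilutes the difference between the arms.
- **Practical effect.** The abstract reports 120 participants as already randomised, so the correction changes no design decision, and confidence intervals will show the precision achieved. That is a reason for a light remedy, not for leaving a wrong power figure in place.

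**Conclusion.** The concern holds. With 60 per group, h = 0.45 and a two-sided 0.05 level, power is 69%, not 80%; 80% would need 78 per group, and 60 per group reach 80% only for h = 0.51. The result rests only on inputs stated in the protocol, and exact calculation at the rates matching the stated risk difference agrees with it (69.2%). No two-sided reading that was tried gives 80%.

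Two further statements are weaker. That a one-sided critical value was used is an inference. The detectable risk difference of about 0.24 to 0.25 assumes a control rate near 0.26 or 0.52. All figures are for a single comparison, before any loss of participants, multiplicity or clustering.

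**What to change.** Keep 120 participants and the two-sided test, and rewrite the power paragraph to say that 60 per group give 69% power for h = 0.45, and 80% power for h = 0.51, at two-sided 0.05. State the control response rate that was assumed, and restate the risk difference and number needed to treat for that rate. If 0.215 is kept, attach it to 69% power; at 80% power it becomes about 0.246 for a control rate of 0.262, or 0.242 for 0.523. Say which way the number needed to treat is rounded.

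Do not relabel the test as one-sided to preserve the 80%. That would loosen the error rate after the participants were randomised.

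The cost is one rewritten paragraph and a less favourable power figure. No extra participants are needed.

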**Methods:**

We randomized 120 over-65 males and females into groups of similar size and timing and will give each either moderate physical activity or cultural and recreational activities. Being younger than 65 years, inability to participate in physical activity for any medical reason, and involvement in a massive program of physical exercise are the exclusion criteria. The primary outcome measures are: quality of life, walking speed, and postural sway. Participants are tested at baseline, post-treatment, and 6-month (24 weeks) and 12-month (48 weeks) follow-ups.

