### Methods to handle missing data

We do not expect many missing data since the study will be carried out within just one center and the interventional trial has a short duration (12 weeks). However, missing data may occur during the follow-up period. Thus, in the primary analysis, missing data will be replaced by “last-observation-carried-forward.” Then, multiple imputations will be used for sensitivity analyses.

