The large number of tests and measurements at multiple time points is the main strength of the study, since this allows investigation on the moderators and mediators of treatment efficacy, a point often neglected in past studies. Nevertheless, the number of tests may pose a challenge to the participants, increasing the risk of dropout at post-treatment and follow-up. Many questionnaires also pose the risk of missing data, which is another limitation of the study. Great care will be given to minimize the risk of dropout and incomplete assessment by periodic meetings with the assessors and clarifications to the participants at each test point. It should be noted the lack of accounting for clustering in the analysis, which might bring some potential limitations. However, in this study, the number of clusters is really low, and accounting for clustering, in this case, might lead to biased estimates of standard errors [27].

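### The 60 per group required for 80% power are exactly the number randomised, so there is no margin for loss, and two-sided power is about 69% even with complete data

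*Protocol article*

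**What the plan says.** Protocol article, Power analysis and statistical analysis: "a sample of 60 participants per group is required to achieve 80% power" with h = 0.45, "at a two-sided significance level of 0.05". The same section gives a risk difference of 0.215 and an NNT of 5. It puts everyone with t0 data into the analysis by treatment allocated.

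Abstract, Methods: "We randomized 120 over-65 males and females". Randomization: "Randomization will be by blocks of randomized permutations to experimental treatment with a 1:1 rate". Together these give 60 per group.

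Two sections speak about loss:
- Methods to handle missing data: "We do not expect many missing data since the study will be carried out within just one center". It then accepts that data may go missing during follow-up, and makes last observation carried forward (LOCF) the primary method, with multiple imputation as sensitivity analysis.
- Discussion: "the number of tests may pose a challenge to the participants, increasing the risk of dropout at post-treatment and follow-up". It also names missing data as a limitation.

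Table 2 makes week 12 a primary time point for SF-12, walking speed and postural sway area, and end of follow-up a second primary time point for SF-12.

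**The concern.** The number required and the number entered are the same, so the stated 80% presumes that every randomised participant contributes the planned information. The article does not clearly expect that. Besides the test burden, it provides for participants to be withdrawn when a new treatment costs them eligibility for physical activity (Procedure and setting) and suspended after certain adverse events (Adverse event reporting and harms).

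The power figure is the only operating characteristic the article states. If it is too high, a null result will be read as stronger evidence of no effect than the trial could give.

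**Working it through.** **Inputs.** From the article: n = 60 per group, h = 0.45, two-sided alpha 0.05, 80% power, risk difference 0.215, all with t0 data analysed, LOCF. Assumed: loss of 5%, 10% or 20%, equal in both arms, with those lost otherwise as likely to respond as those who stay. Response is taken to mean a positive improvement from baseline, in line with the expected improvements of 10%, 10% and 20% listed for the three outcomes.

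**Step 1: the stated figure.** For Cohen's h, n = 2 × ((z_alpha + z_beta)/h)².
- Two-sided: 2 × ((1.960 + 0.842)/0.45)² = 77.5, so 78 per group.
- One-sided: 2 × ((1.645 + 0.842)/0.45)² = 61.1, so 62 per group.

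Power = Phi(h × sqrt(n/2) − z_alpha), and h × sqrt(60/2) = 0.45 × 5.477 = 2.465.
- Two-sided: Phi(2.465 − 1.960) = 69.3%.
- One-sided: Phi(2.465 − 1.645) = 79.4%.

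The stated 60 per group for 80% power is not reproduced for the two-sided test. It agrees closely only with a one-sided 0.05 test.

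**Step 2: week-12 loss under the planned rule.** A participant lost before week 12 has only the baseline value. Carried forward, it gives zero change and hence no response. The analysed n stays at 60, but each arm's response proportion is multiplied by (1 − d). Two pairs of proportions give both h = 0.45 and a difference of 0.215: 0.262 v 0.477 and 0.523 v 0.738.

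Example at d = 10%:
- 0.2358 v 0.4293 gives h = 0.415, and Phi(0.415 × 5.477 − 1.960) = 62%.
- 0.4707 v 0.6642 gives h = 0.393, and Phi(0.393 × 5.477 − 1.960) = 58%.

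To see what loss does on its own, grant the article its 80% by setting the noncentrality to 1.960 + 0.842 = 2.802 at no loss, and scale it by the ratio of diluted to undiluted h.

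| Loss by week 12 | h, lower pair | h, higher pair | Two-sided power | If 80% is granted |
|---|---|---|---|---|
| 0% | 0.450 | 0.450 | 69% | 80% |
| 5% | 0.432 | 0.420 | 63–66% | 74–77% |
| 10% | 0.415 | 0.393 | 58–62% | 69–73% |
| 20% | 0.381 | 0.346 | 47–55% | 58–66% |

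**Step 3: comparison with dropping the cases.** If those lost were simply left out, n would be 57, 54 or 48, and two-sided power 67.1%, 64.7% or 59.7% (78.0%, 75.7% or 70.7% from a granted 80%). Keeping n at 60 through LOCF therefore does not protect power at week 12; under these assumptions it costs more than losing the cases.

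**Step 4: end of follow-up.** A participant lost after week 12 carries the week-12 SF-12 value. If the effect fades after treatment, this could preserve or enlarge the apparent difference; if it grows, it could shrink it. The article gives nothing from which to fix the direction, so no figure is offered.

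**The case against.** The case on the other side has force in several places.

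- **No rate is given.** The Discussion names a risk and predicts no amount. A reader might infer that dropout alone makes 80% unattainable at both primary time points. The documents do not support that: from a granted 80%, 5% loss costs only about 2 points if cases are dropped and about 3 to 6 under LOCF.
- **Dropout is not the main cause.** Most of the shortfall, from 80% to 69%, is there with complete data and comes from the sidedness of the calculation. Adding an allowance to 60 would not restore 80%.
- **The planned analysis keeps everyone with t0 data.** That is so, and completer figures alone would misdescribe it. But the loss then acts through dilution of the effect, which Step 2 measures.
- **A low expectation and an acknowledged risk can coexist.** The article also describes mitigation: session reminders, discussion of skipped sessions, meetings with assessors, and a test load set from past pilot studies. A reader might infer an outright contradiction on loss. It is a tension, confined mainly to post-treatment, where one section expects little missing data and the other sees a raised risk.
- **A condensed article may leave a dropout rate to the full protocol.** The absence of a rate is accordingly not the point. The article itself fixes the required number, the number randomised and the power, and those three leave no margin.

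**Conclusion.** The point holds in this form: 60 per group contains no allowance for loss, and the 80% is not delivered as stated. Two-sided power is about 69% with complete data, a result that needs no assumption beyond the article's own inputs. At week 12, under the planned LOCF rule, it falls to about 63–66%, 58–62% and 47–55% at 5%, 10% and 20% loss. Those ranges rest on assumed loss rates equal in both arms, on baseline carried forward counting as non-response, and on the two response pairs that match the stated 0.215. A reader might also infer that follow-up SF-12 is the worst affected. That cannot be said, because the effect of LOCF there depends on what is carried.

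**What to change.** In Power analysis and statistical analysis:
- restate the two-sided power at 60 per group and h = 0.45 as about 69% with complete data;
- add the week-12 power under the planned LOCF rule at stated, assumed loss rates, for example 5%, 10% and 20%;
- say that 60 per group contains no allowance for loss;
- say that this calculation does not establish power for SF-12 at end of follow-up.

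In Methods to handle missing data, reconcile the expectation of few missing data with the post-treatment dropout risk named in the Discussion.

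The cost is a few sentences and a less favourable stated power. Randomisation, enrolment and the analysis are unchanged.
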